#### Interventions

Each RCT group consists of one or a combination of the following components as the intervention. The detail is shown in Table 1.

**Table 1 Tab1:** Summary of intervention in 3 groups

	HAR Group	Text Group	Control Group
Onsite active referral + tailored messages	✓		
Text messaging		✓	
AWARD advice + health warning leaflet + referral card + self-help booklet	✓	✓	
General brief advice + self-help booklet			✓

#### On-site active referral for HAR group

Interventions in HAR group are designed to promote the use of the existing SC services to increase abstinence. Five major cessation services in Hong Kong will be involved. They had successful collaboration with the Contest in 2015, and their characteristics were reported previously [11, 25]. Well-trained SC ambassadors will assist on-site booking for SC services based on participants’ preferred services providers and available time. For participants who are not ready to seek SC services at on-site, they will be encouraged to set a date for appointment booking. SC ambassadors will follow them through the telephone at 1 week. They can also inform us through instant messages or telephone calls anytime between 1-week and 1-month. SC ambassadors will help participants book the appointment once receiving their decisions on SC services providers, preferred time and clinics.

#### Tailored messages for HAR group

Tailored, automatic, and fix-schedule messages will be sent once per day for the first month (or stop upon request by the smokers) via instant messaging (IM) services (e.g., WhatsApp, WeChat) since initial contact. For smokers who do not use or refuse to receive IM messages, they will be contacted via short messaging service (SMS) or telephone calls. Contents of the tailored messages will be developed through a qualitative study using open-ended questions in participants of QTW 2014. Tailored messages will include (1) brief health warning, (2) benefits of quitting, (3) SC services and their effectiveness (4) story about pleasant experiences and successful quitting of smokers in the past, and (5) readiness to make and be adherent to SC appointments.

Details of successfully booked SC appointment, such as SC services address, contact information, date, and appointment number will be delivered to the smokers using messages or telephone calls. All smokers will receive a reminder-to-attend message or telephone call 1–3 days before the appointment date. Research staff will monitor the use of SC services by smokers at each follow-up (1-, 2-, 3- and 6-months) and assist participants to book or re-book the appointments if necessary. We shall liaise with the existing service providers and seek their assistance in helping the smokers in a timely manner.

#### Text messaging for Text group

The text-messaging intervention aims to motivate smokers to book the SC appointments by themselves. They will be introduced (using the referral card) and motivated to use the SC services at onsite. IM/SMS messages (3 per week in the first month, then 1 per week in the second month) will be sent to encourage them to book an SC appointment since initial contact. A total of 16 messages will be sent to the smokers. The messages will be simpler and more generic than the messages in HAR group. Research staff will monitor the SC services use at each follow-up (1-, 2-, 3- and 6-months) and encourage smokers to book or re-book the appointment if necessary. This is a much cheaper and brief method than HAR group.

#### AWARD advice for HAR and Text groups

AWARD model-guided advice will be delivered to smokers onsite, which include (1) ask about smoking history, (2) warn the subject about the increased risk of premature death (with a brief health warning leaflet, see below for information), (3) advise the subject to quit immediately, (4) refer the subject to existing cessation services (with a referral card, see below for information), and (5) do it again if the subject fails to quit. The whole process of AWARD can be delivered within 30 s to 1 min. The model has been validated in our previous trials [11, 17–20].

#### Self-help materials

Following the previous trial in 6th QTW in 2015 [25], the 2-side health warning leaflet, which systematically covers the most important messages to motivate SC, as well as the pocket size referral card will be disseminated to the smokers in the 2 intervention groups. The content of referral card includes brief information and highlights of existing SC services, contact details, available therapies, and incentive information.

All participants in 3 groups will receive a 12-page self-help booklet developed by the COSH. The content includes information about benefits of quitting, smoking and diseases, methods to quit, how to handle withdrawal symptoms, declaration of quitting, etc.

#### General brief advice for Control group

Participants in the control group will receive very brief, minimal and general SC advice, such as “Please quit smoking for improving health and save money”, “Please refer to the self-help booklet for the details about smoking cessation” and “Please call us if you have any enquiry”.

### Data collection

#### Baseline

The baseline questionnaire data includes four parts and will be collected by trained SC ambassadors. The first part measures participants’ smoking status (e.g., average number of cigarettes smoked per day, the age of starting smoking and the usual time having the first cigarette smoked each day, attempts to quit or reduce, methods used in past quitting attempts, etc.). The second part measures participants’ readiness to quit, and perceived importance, difficulties and confidence to quit smoking. The third part asks participants’ knowledge about smoking (e.g., e-cigarette and risk of smoking). The final part collects sociodemographic data (e.g., sex, age, education level, number of children, occupation, marital status, annual income, etc.).

#### Follow-up

The follow-up surveys will be conducted by telephone at 1, 2, 3 and 6 months after the baseline. A set of questionnaire similar to the baseline questionnaire will be used to collect information on smoking behavior, quit attempts, smoking-related psychological factors and perceived social support in the quitting process, and the use of referred SC services. Participants who reported 7-day PPA at 3 and 6 months will be invited for a biochemical validation using the exhaled carbon monoxide (CO) and saliva cotinine tests.

#### Outcome assessments

The primary outcome is self-reported 7-day PPA at 3 and 6 months.

Secondary outcomes include:SC services use: calling a hotline of the SC services, booking an appointment, SC clinic attendance, counselling session attendance, and other indicators to be further specified after liaison with the existing SC services (e.g. services providers’ records on services utilization). The number of referrals will be calculated for the baseline and 1-, 2-, 3- and 6-month follow-ups.Biochemically-verified past 7-day PPA using exhaled-air CO levels < 4 ppm and saliva cotinine concentration < 10 ng/ml [26, 27].Smoking reduction is defined as daily cigarette consumption reduction by > 50% compared with baseline.

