**Methods/design:**

This is a single-blind, parallel 3-armed cluster randomized controlled trial (cRCT) consisting of high-intensity SC active referral (HAR Group), low-intensity SC referral by text messaging on promoting SC services use (Text Group) and a control group receives general very brief advice. Biochemically validated daily smokers will be proactively recruited in the community from 68 clusters (recruitment sessions). The primary outcome is self-reported 7-days point prevalence abstinence (PPA) at the 3- and 6- month follow-ups. Secondary outcomes are SC service use, smoking reduction rate (SRR, daily cigarette consumption reduced by ≥50%; excluding quitters) and biochemically validated quit rate (exhaled CO < 4 ppm and salivary cotinine < 10 ng/ml). Outcome assessors and data analysts will be blinded to group allocation. Intention-to-treat principle and Generalized Estimating Equation (GEE) regressions will be used for data analysis.

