### Sample size and power analysis

The computer program G*Power is used to calculate the sample size [24]. The proposed sample size is based on the primary outcome of self-reported 7-day point prevalence of abstinence (PPA) at 3 months. Based on the QTW study in 2015, the 3-month PPA for the moderate-intensity active referral intervention and the control group was 18.7 and 14%, respectively [11]. Therefore, the effect size (odds ratio) for the intervention in the present study is set conservatively at 1.33. To detect a significant difference in quit rate with a power of 80% and a significance level of 5%, 971 participants in each arm are required. Given the limited resources and recruitment period, the maximum total sample size is 1200 (400 per group). The *p*-value and the power for testing the expected effect size (1.54) will be 0.08 and 57.3%.

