### Data analysis

Data will be entered into SPSS for Windows (version 23). Descriptive statistics such as frequency, percentage, and mean will be used to summarise the outcomes and other variables. The main analysis will be a comparison between both intervention groups and the control group for the proportions of smoking abstinence at 3 and 6 months, using chi-square tests and odds ratios with 95% confidence intervals. Generalized Estimating Equation (GEE) models will be applied to test the intervention effect, to identify the baseline predictors of successful quitting and to assess the changes in smoking-related factors over time. Intention-to-treat (ITT) analysis will be used in which participants who lose contact or drop out in the follow-ups will be treated as a failure to achieve any cessation outcome. Multiple imputations will be used to compute missing data for outcome variables.

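### The primary outcome is set at both 3 and 6 months for two arms against control, but sized as one 5% comparison at 3 months, with no statement of how the time points combine

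*Protocol article*

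**What the plan says.** All references are to the protocol article. Two places define the primary outcome at two time points. The Abstract (Methods/design) states: "The primary outcome is self-reported 7-days point prevalence abstinence (PPA) at the 3- and 6- month follow-ups". The Outcome assessments section repeats it: "The primary outcome is self-reported 7-day PPA at 3 and 6 months".

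The Sample size and power analysis section refers instead to "the primary outcome of self-reported 7-day point prevalence of abstinence (PPA) at 3 months". It takes 18.7% and 14% as the earlier 3-month rates and requires 971 per arm for 80% power at a 5% level. It then caps the trial at 1200 (400 per group) for reasons of resources and recruitment time, and states a power of 57.3% for an effect size of 1.54.

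The Data analysis section describes the main analysis as a "comparison between both intervention groups and the control group for the proportions of smoking abstinence at 3 and 6 months". The tests named there are chi-square tests, and effects are to be reported as odds ratios with ordinary 95% intervals. It adds that "Generalized Estimating Equation (GEE) models will be applied to test the intervention effect", without ranking these models against the chi-square tests or tying them to a time point.

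No section says whether success means either time point or both, which arm comparison carries the conclusion, or how the 5% is shared.

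**The concern.** Two arms, each compared with control at two times, make four primary comparisons. The sample size section allows for one. Under an either-time rule, an ineffective intervention gets more than one chance to be declared effective, and the false-positive rate for the primary claim exceeds 5%. Under a both-times rule that problem goes, but the chance of success is lower than for the single comparison whose power is quoted. The reader cannot tell which error rate or which power belongs to the trial's main conclusion. If the two time points disagree, nothing in the article says what the conclusion would be.

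**Working it through.** **1. The plan's own figure.** Inputs from the sample size section: p1 = 0.14, p2 = 0.187, level 5% (two-sided reproduces the figure), power 80%. With the mean rate p = 0.1635,

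n = [1.960·√(2p(1−p)) + 0.8416·√(p1(1−p1) + p2(1−p2))]² / (p2 − p1)²

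= [1.960 × 0.5230 + 0.8416 × 0.5219]² / 0.047² = 2.1443 / 0.002209 = 970.7, so 971 per arm.

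This matches exactly. The 971 is therefore one arm against control, at 3 months, at 5%, with no 6-month input and no allowance for a second test.

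**2. False-positive rate.** Assumptions: each test is two-sided at 5% and holds that level on its own. Equal arms with a shared control give a correlation of 0.5 between the two arm comparisons. The correlation r between the 3- and 6-month statistics is not in the article, so it is varied. The one-arm column is the bivariate normal probability that |Z| exceeds 1.96 at either time. The four-test columns are simulated (2,000,000 draws).

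| r | One arm, either time | Two arms, either time | Two arms, either time, false benefit only |
|---|---|---|---|
| 0.3 | 9.5% | 16.9% | 8.5% |
| 0.5 | 9.1% | 16.2% | 8.1% |
| 0.7 | 8.3% | 14.9% | 7.5% |
| 0.85 | 7.5% | 13.3% | 6.7% |

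The last column compares with a nominal 2.5% for one test. Two arms at a single time point give 9.1% two-sided. As a bound, four independent tests would give 1 − 0.95⁴ = 18.5%.

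**3. Power under the two possible rules.** The article gives earlier-trial rates at both times: 14% v 18.7% at 3 months (sample size section) and 11.5% v 17.2% at 6 months (Background). At 400 per arm and two-sided 5%, the power is 43.5% at 3 months and 63.3% at 6 months. For one arm, with r from 0.3 to 0.85:

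- both times significant: 32% to 41%;
- at least one significant: 75% to 65%.

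The stated 57.3% is for a single comparison at effect size 1.54. Read as an odds ratio on 14% (20.0%), I obtain 62.4% without and about 59% with a continuity correction. On either calculation it describes one test, not a rule over two time points.

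**4. Price of adjusting.** At 2.5% (the first Holm step for two tests), 14% v 18.7% needs 1176 per arm rather than 971. Power at 400 per arm falls from 43.5% to 32.8%. At 1.25% (the first step for four tests) the figures are 1380 per arm and 24.1%.

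**The case against.** **The rule may be elsewhere.** A journal article condenses the full protocol, and a multiplicity rule may sit in an analysis plan not shown. That is fair, and the absence of a rule alone would not be a finding. What remains is that the article gives its primary outcome as two time points in two places and as one in a third, and sets out main comparisons that outnumber the one it sized.

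**Four tests at 5% is a reading.** A reader might infer that the plan assigns 5% to each of four tests. No sentence does. The reading comes from the 5% used for sizing and the ordinary 95% intervals in the analysis. The chi-square comparison could be a three-group test at each time, and a GEE model could cover both times. The article does not say so, and does not rank the two methods. The percentages are conditional on the four-test reading.

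**Pooling two interventions is disputed.** Many statisticians would not adjust across distinct interventions that share a control. If that is granted, the 13% to 17% drops out, but 7.5% to 9.5% per intervention remains, because it comes from the two time points alone.

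**Sizing on 3 months does no harm at 6 months.** This stands for a single 5% test. The Background rates need 593 per arm at 6 months, fewer than 971. Nor does the actual 1200 rest on the 5% calculation; resources set it.

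**Selecting the time point afterwards.** A reader might infer that the investigators could quietly choose the better result. The documents do not support that: both times are declared primary and the main analysis commits to both, so an omission would show. The gap is in how a split result is to be read.

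**Conclusion.** The concern holds in limited form. The article's definitions of the primary outcome do not agree with the sample size section, and the main analysis as written leaves more than one unadjusted route to a positive primary claim.

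Under an either-time rule, the two-sided error is about 7.5% to 9.5% per intervention, or about 13% to 17% if both arms form one family. These figures rest on an inferred 5% per test, an assumed between-time correlation of 0.85 to 0.3, and individual tests that hold their level. Under a both-times rule there is no inflation for an arm, and the fault is that the quoted power belongs to a different rule.

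The article does not support the stronger conclusion that the trial has a 13% to 17% error rate as a settled fact. Nor does it support testing the high-intensity arm before the text arm: the aims give the two interventions equal standing.

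**What to change.** Name one primary time point in the Abstract, Outcome assessments and Data analysis sections, and make the other the first secondary outcome. Three months is the choice consistent with the sample size section. If both are to stay primary, state that either suffices and apply Holm across the two times, or state that both are required and quote the power for that rule.

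Say whether each intervention is a separate claim or the two arms form one family. If one family, apply Holm to the two arm-against-control tests at the primary time point, or to all four tests if both times stay primary. A fixed order between the arms would need a reason that the article does not give.

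The cost is mainly wording. With one primary time point, 6 months loses its co-primary status. With Holm, the first step is tested at a smaller level: for 14% v 18.7% at 400 per arm, power at that step is 32.8% for two tests or 24.1% for four, against 43.5% unadjusted.

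The trial was registered in June 2016 and set in the 2016–17 Contest, so demoting a declared primary time point is itself an outcome change. It should be dated and reported as made before unblinded results were seen; a change that cannot be shown to meet that condition should be labelled post hoc.

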## Background

Despite decades of public health education and interventions on smoking cessation (SC), tobacco use remains the leading cause of preventable death causing over 7 million deaths worldwide every year [1]. Recent data indicates a decrease in the overall smoking prevalence but still with around 615,000 daily cigarette smokers in Hong Kong in 2017 [2]. Evidence has shown that smokers received SC services increases successful rate in quitting [3–6]. Although a variety of free SC services (e.g. quit-lines, clinics) are available in Hong Kong, the utility rate is low and only 14.2% of smokers had ever used [2]. Low-cost, easy accessibility and effective SC services are warranted to provide advice, medication, and support for people to quit smoking [7].

Referring smokers to SC services is one of the cheap and scalable strategies that can maximize usage of public cessation counselling and treatment. Most of current SC services depend on passive referral strategies that require smokers to seek assistance on their own, such as calling the quit-line or attending the SC clinics [8]. Unlike passive referrals that rely on smokers’ self-initiation, active referral emphasizes physicians or other healthcare professionals efforts to refer smokers to SC services directly [9, 10]. Allowance for smokers to choose their preferred service providers and cessation methods might also improve smokers’ engagement in the service and hence enhance the outcomes [11]. Proactive referral approach can help overcome the barrier of self-initiation as most community smokers quit on their own without SC services [12]. Our previous randomized controlled trial (RCT) showed that moderate active referral of SC services significantly increased smoking abstinence rate at 6 months when compared with brief general SC advice (17.2% vs. 11.5%, *p* = 0.02) [11].

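### Validated abstinence makes no allowance for nicotine-containing medication, so the validated quit rate would be biased against HAR if such use at the test is more common there than in control

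*Protocol article*

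**What the plan says.** Under Outcome assessments, the protocol article lists as a secondary outcome 7-day abstinence verified by "exhaled-air CO levels < 4 ppm and saliva cotinine concentration < 10 ng/ml". The Abstract gives the same two limits, again joined by an and. Under Follow-up, "Participants who reported 7-day PPA at 3 and 6 months will be invited for a biochemical validation", using both the breath and the saliva test. No section states a different rule for participants taking nicotine-containing medication.

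Three other places bear on who might be taking it:

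- Background, on services in general: "SC services are warranted to provide advice, medication, and support for people to quit smoking".
- On-site active referral for HAR group: "Interventions in HAR group are designed to promote the use of the existing SC services to increase abstinence".
- Self-help materials: the referral card, given to HAR and Text but not to control, covers "contact details, available therapies, and incentive information".

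The primary outcome does not involve cotinine: "The primary outcome is self-reported 7-day PPA at 3 and 6 months".

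**The concern.** Cotinine is a breakdown product of nicotine whatever its source. This is general pharmacology and is not stated in the article. A participant who has stopped smoking but takes nicotine-containing medication can therefore pass the CO test, fail the cotinine test and be recorded as not abstinent.

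Such errors matter most when they fall unequally across arms, and the design gives a reason to expect that. HAR offers on-site booking, a call at one week, and staff help with booking or re-booking at 1, 2, 3 and 6 months. Text encourages participants to book for themselves. Control receives brief advice and a booklet. Smokers already following another cessation programme are excluded, so a difference in treatment use would arise mainly after randomization, and raising service use is the purpose of HAR.

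At stake is the only biochemical measure of abstinence. The primary outcome is self-report by participants who cannot be fully blinded, although assessors and analysts are. Readers will look to the validated rate to confirm the primary result. If that rate is pulled down in HAR by treatment rather than by smoking, it could seem to contradict a real benefit.

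**Working it through.** **The plan's own figures.** The article gives no expected validated rate and no figure for the cotinine criterion. Its planning rates are 18.7% (intervention) and 14% (control) self-reported abstinence at 3 months. They reproduce the stated 971 per arm with a two-sided 5% test, 80% power and no continuity correction:

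n = [1.960 × √(2 × 0.1635 × 0.8365) + 0.8416 × √(0.187 × 0.813 + 0.14 × 0.86)]² / 0.047² = 970.7, rounded up to 971.

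This confirms the reading of the rates. It concerns the self-reported outcome and neither supports nor weakens the present point.

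**Inputs for the illustration.**

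- True abstinence: 18.7% in HAR and 14% in control, borrowed from Sample size and power analysis. Using them as true rates is an assumption.
- h and c: the shares of abstainers in HAR and control whose cotinine is at or above 10 ng/ml at the test because of medication. The article gives neither, so both are assumed over a range.

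**Formulas.** Observed rate = true rate × (1 − share). Odds ratio (OR) = [p₁/(1 − p₁)] / [p₀/(1 − p₀)].

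With no medication use: (0.187/0.813)/(0.14/0.86) = 0.2300/0.1628 = 1.41.

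With h = 20% and c = 5%: 0.187 × 0.80 = 0.1496 and 0.14 × 0.95 = 0.1330, so OR = (0.1496/0.8504)/(0.1330/0.8670) = 1.15.

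| h (HAR) | c (control) | Observed HAR | Observed control | Observed OR |
|---|---|---|---|---|
| 0 | 0 | 18.7% | 14.0% | 1.41 |
| 5% | 0 | 17.8% | 14.0% | 1.33 |
| 10% | 2% | 16.8% | 13.7% | 1.27 |
| 20% | 5% | 15.0% | 13.3% | 1.15 |
| 30% | 5% | 13.1% | 13.3% | 0.98 |
| 10% | 10% | 16.8% | 12.6% | 1.40 |
| 20% | 20% | 15.0% | 11.2% | 1.39 |

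The 1.33 in the second row matches the effect size quoted in the article only by coincidence.

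**Break-even.** The observed rates are equal when 0.187(1 − h) = 0.14(1 − c). With c = 5%, h = 1 − 0.133/0.187 = 29%.

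**Lower true rates.** Validated rates may well be lower than self-reported ones. Assuming 8% v 6% (OR 1.36) and c = 5%, HAR shares of 10%, 20% and 30% give observed rates of 7.2%, 6.4% and 5.6% against 5.7%, so ORs of 1.28, 1.13 and 0.98. The pattern is the same.

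The last two rows of the table show what drives the result: a difference in use between arms at the time of the test. Use that is common but equal lowers both rates and barely moves the OR.

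**The case against.** The strongest reply is that the article does not show the bias exists. It never names nicotine replacement. The Background remark is about cessation services in general, the referral card entry gives no type of therapy, and the characteristics of the five collaborating services are left to cited reports. Nothing is said about how long treatment lasts, whether abstainers would still use it at 3 or 6 months, or what control participants obtain elsewhere. This stands. A reader might infer that the rule does bias the validated rate against HAR, or that the direction holds whatever the shares. The documents support neither, because the bias needs unequal use at the test and the scenarios assume that inequality. Timing leaves the possibility open: a booking made at the 2-month contact could mean treatment under way at 3 months. The case at 6 months is weaker.

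Text participants receive the same advice model and referral card as HAR, plus messages urging them to book. Text v control could therefore be affected too, and the gap between HAR and Text may be small. That also stands.

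Requiring both tests is the conservative choice, and waiving cotinine for reported users lets self-report override a test, perhaps more often in HAR. This is a sound reason not to replace the strict rule. It is no reason against reporting a second rate beside it.

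A CO-only rate for everyone could be computed from the tests already planned. It would, however, discard cotinine for untreated participants too, and the planned question on use of referred services does not identify medication use at the test.

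The comparison is imprecise in any case: 8% v 6% with 400 per arm (32 v 24 people) has roughly 20% power, ignoring clustering. That limits what the outcome can show but does not excuse a systematic error in it.

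Last, a full protocol may cover the matter. But the rule is printed twice with numeric limits. As printed, it gives the wrong answer for a treated abstainer, so this is more than an omitted detail.

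**Conclusion.** The point holds in conditional form. As written, the rule counts an abstainer whose cotinine is raised by nicotine-containing medication as not abstinent. The design makes such use plausibly more common in HAR, and to a lesser degree in Text, than in control. If so, the validated quit rate is biased against HAR.

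The size is unknown. Under assumed shares of 5–30% in HAR and 0–5% in control, a true OR of 1.41 would appear as 1.33 down to 0.98. With equal shares it stays at 1.39–1.40. A reader might take the 0.98 as showing that the effect disappears, but it is the far end of an assumed range and not a forecast.

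The matter is confined to a secondary outcome. Self-reported abstinence, the primary outcome, is untouched.

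**What to change.** Record use of nicotine-containing medication at the validation visit, with the same question in all three arms. Prespecify and report two validated rates, each applying one rule to every arm:

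1. the strict rate: CO < 4 ppm and cotinine < 10 ng/ml for everyone tested;
2. a rate in which participants reporting nicotine-containing medication are classified by CO < 4 ppm alone, and all others by both tests.

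State that a lower strict rate in HAR will not be read as contradicting the self-reported result unless the second rate is shown beside it.

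The cost is one question and a few sentences in the outcome definition, since both tests are already planned. The downside is that CO has a shorter detection window and the exception relies on reported medication use, so some recent smokers could be counted as abstinent. Reporting both rates bounds this: the strict rate may count too few treated quitters, and the second may count too many.
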